# The effect of combining manual therapy with exercise for mild chronic obstructive pulmonary disease: study protocol for a randomised controlled trial

**DOI:** 10.1186/s13063-017-2027-z

**Published:** 2017-06-17

**Keywords:** Chronic obstructive pulmonary disease, COPD, Manual therapy, Spinal manipulative therapy, Pulmonary rehabilitation, Exercise, Randomised controlled trial, Lung function, Trial protocol

## Abstract

**Background:**

Chronic obstructive pulmonary disease (COPD) is a major cause of disability and hospital admission. Current management strategies have not been successful in altering the loss of lung function typically seen as the disease progresses. A recent systematic review into the use of spinal manipulative therapy (SMT) in the management of COPD concluded that there was low level evidence to support the view that a combination of SMT and exercise had the potential to improve lung function more than exercise alone in people with moderate to severe COPD.

The aim of this study is to investigate whether the combination of exercise and manual therapy (MT) that includes SMT produces sustainable improvements in lung function and exercise capacity in people with mild COPD.

**Methods/design:**

The study is a randomised controlled trial of 202 people with stable mild COPD. The cohort will be divided into two equal groups matched at baseline. The first group will receive a standardised exercise program. The second group will receive MT that includes SMT plus the same standardised exercise program. Exercise will be administered a total of 36 times over an 18-week period, while MT will be administered in conjunction with exercise a total of 15 times over a 6-week period. The primary outcome measure is lung function (forced expiratory volume in the 1^st^ second: FEV_1_ and forced vital capacity: FVC). The secondary outcome measures are the 6-minute walking test (6MWT), quality of life questionnaire (St George’s Respiratory Questionnaire: SGRQ), anxiety and depression levels (Hospital Anxiety and Depression Scale: HADS), frequency of exacerbations, chest wall expansion measurements (tape measurements) and systemic inflammatory biomarker levels. Outcome measurements will be taken by blinded assessors on seven occasions over a 48-week period. Adverse event data will also be gathered at the beginning of each intervention session.

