### Consent process

The consent process followed in this trial will be the same for all participants. Potential participants will receive the Patient Information and Consent Form (PICF) explaining the trial’s processes and procedures, including consent to publish, and what is expected from them during the trial. Each participant will be given the opportunity to ask questions about their involvement in the trial and to have those questions answered by a researcher associated with the trial prior to providing consent. A trial-specific ID number will be used when gathering and recording all information about a participant. A list containing the contact details of all participants and their corresponding ID numbers will be kept separate from all other data. All paper copy forms will be stored in a locked filing cabinet in the hospital facility during the trial. Once the intervention phase of the trial has been completed (week 26), all data from these files will be transferred to a password-protected encrypted file and stored on the chief investigator’s university computer located in his locked university office. These files will be backed up on an external hard drive and stored in a locked filing cabinet in the university office of another investigator. The trial was approved by the South Eastern Sydney Local Health District - Human Research Ethics Committee (HREC): approval number 13/004.

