### Statistical analysis

Data will be reported as group means, standard deviations and 95% confidence intervals. Analysis will be performed as an analysis of covariance (ANCOVA) for differences between groups with baseline as a covariate. Standard errors will be calculated using a non-parametric bootstrap to allow for the different error variances for each group. A *p* value of < 0.05 has been set for statistical significance. For outcomes found to be statistically significant, the proportion of participants with a change greater than the minimum clinically important difference will be calculated for each outcome. The number needed to treat will be calculated using Bender’s method for confidence intervals. Missing data will be accounted for by using an intention-to-treat analysis with data from subjects lost to follow-up imputed using the multiple imputation method.

Two interim analyses are planned before the final analysis. They are mid-trial following the second blood test (week 24) and 6 weeks after completion of all interventions (week 32). The conduct of the trial will not be affected by the results of these interim analyses.

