### Adverse events

The risks of harm or discomfort to participants in this project primarily relate to the potential for adverse events (AEs) resulting from MT intervention. The majority of reported AEs associated with MT are mild (muscle soreness and local discomfort), self-limiting, require no further medical attention and resolve within 48 hours [25]. Moderate AEs such as fracture, have also been reported following SMT and have been estimated to occur at a rate of 1 in 40,000 [26]. Reports of major or catastrophic AEs resulting from spinal manipulation have appeared in the literature with nearly all associated with neck (cervical) manipulation. This trial involves manipulation of the thoracic spine and ribs only and does not include any neck manipulation. The MTP used in this trial is the same protocol as the one used in two previous trials on people with COPD [22, 23]. There were no major or moderate AEs reported in either of those trials. Mild AEs associated with MT intervention were reported at a rate of 15% (18 out of 112) in the trial on patients with moderate COPD (average age 56.1 years) [22] and at a rate of less than 1% (2 out of 403) in the trial on patients with moderate to severe COPD (average age 65.5 years) [23].

As the MTP used in the trial being reported here is the same as the one used in the two previous Australian trials, it is reasonable to predict that the risk of harm or discomfort to participants will be at a similar rate to those of the previous trials.

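### The only stated adverse-event collection point is the start of an intervention session, so harm capture depends on further attendance and none is stated for weeks 26 to 48

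*Protocol article*

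**What the plan says.** The collection rule is one sentence in the abstract, under Methods/design: "Adverse event data will also be gathered at the beginning of each intervention session". The Adverse events section of the main text describes the expected risks of manual therapy (MT) and the rates seen in two earlier trials, but gives no collection procedure.

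The timetable around that rule is as follows.

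- Exercise, both arms (abstract): "Exercise will be administered a total of 36 times over an 18-week period".
- MT, combined arm only (abstract): "MT will be administered in conjunction with exercise a total of 15 times over a 6-week period".
- Follow-up (abstract): "Outcome measurements will be taken by blinded assessors on seven occasions over a 48-week period".
- End of interventions (Consent process): "Once the intervention phase of the trial has been completed (week 26".
- Second interim analysis (Statistical analysis): "6 weeks after completion of all interventions (week 32".

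Two other provisions bear on safety. Protocol description has exacerbations collected by questioning participants directly, as an outcome. Data monitoring sets up a safety board that meets every 4 months or when needed.

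**The concern.** A question put at the start of a session looks backwards, to the time since the previous session. It works for participants who keep coming. A participant who stops has no later session, so the interval after the last one attended has no stated route into the data. If an event was the reason for stopping, it lies in exactly that interval.

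This matters because the Adverse events section places the trial's risk mainly with MT, which only one arm receives. A harm comparison between arms, and the safety board's view of it, rests on the events that were collected. If collection depends on tolerating treatment, the events most relevant to tolerability are the ones most exposed to being missed. Outcome visits continue after the sessions end, so contact with participants exists in that period, but the article does not say that it is used to ask about harms.

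**Working it through.** No power or sample-size figure is involved. The check is of the timetable and of which intervals the stated question reaches.

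**1. End of interventions.** Statistical analysis puts the second interim analysis at week 32, six weeks after all interventions end: 32 − 6 = week 26. Consent process also gives week 26, so the two sections agree.

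**2. Follow-up without a session.** Outcome visits run to week 48: 48 − 26 = 22 weeks, and 22/48 = 45.8%, or 46% of follow-up. No adverse-event collection point is stated for those weeks.

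**3. Reach of the question while sessions run.** An event after session k is asked about at session k + 1. A participant who attends m sessions has m post-session intervals, of which m − 1 are followed by a question.

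- Full attendance, m = 36: 35/36 = 97.2% of intervals are covered.
- A participant who stops after session m: the uncovered share is 1/m, and it is always the last interval.

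Coverage is therefore high for completers. The uncovered interval is not a random one for participants who stop because of an event: it is the one that contains the event.

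**4. Events after the last MT session.** MT occupies 15 sessions in 6 weeks and exercise 36 sessions in 18 weeks. If exercise continues after the MT course, an event after the final MT session is still asked about at the next exercise session. Whether it does depends on the participant-flow and SPIRIT figures, which are not shown.

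**5. Other contacts.** The exacerbation question covers a disease outcome and would not by itself pick up musculoskeletal harms, such as the fracture named in the Adverse events section. The safety board reviews data already collected and is not a collection route.

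**6. Printed prior rate.** The Adverse events section states: "Mild AEs associated with MT intervention were reported at a rate of 15% (18 out of 112". The division gives 18/112 = 0.1607, or 16%. The other prior rate, 2/403 = 0.0050, agrees with the article's description of less than 1%.

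**The case against.** The strongest reply is that the source is one sentence in the abstract of an article that condenses a longer protocol. The sentence uses the word also, which adds adverse events to the outcome measurements and excludes nothing. Spontaneous reports, follow-up of withdrawals and questions at later visits may all be in the full protocol, the figures or the additional file. The trial runs in a hospital department, with seven outcome visits and a safety board. This stands in part. It rules out any claim that other routes are absent, but the one schedule the article commits to still depends on attendance.

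Several stronger readings are tempting and are not supported:

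- **That events which stop participation are never recorded, or have no chance of capture.** Nothing says that a volunteered event, or a reason given for stopping, would go unrecorded.
- **That a number of missed events follows from the 10% drop-out.** That figure is a sample-size allowance. The article does not link it to adverse events, and it does not say that someone who stops sessions also leaves outcome follow-up.
- **That the comparison is shown to be biased in favour of MT.** Sessions occur in both arms, so the stated question covers both. Weeks 26 to 48 contain no intervention, and the Adverse events section says that most MT-related events resolve within 48 hours. A differential bias is possible but not demonstrated.
- **That the safety forecast is unusable as a benchmark because the two prior rates differ widely.** The article says "it is reasonable to predict that the risk of harm or discomfort to participants will be at a similar rate" with reference to both trials, prints both rates with their populations, and uses neither in a stopping rule or an analysis. The 15% is a clerical slip.

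**Conclusion.** The point holds as a weakness in the stated schedule. The single collection point given makes harm ascertainment conditional on attending a further session. It leaves two gaps: the interval after each participant's last attended session, and the 22 weeks (46% of follow-up) from week 26 to week 48. Events that end participation could be under-counted.

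The number of events affected, and any difference between arms, cannot be computed from the article. The conclusion assumes that the abstract's sentence is the working schedule. If the full protocol already provides other routes, the point reduces to stating them. The 15% should read 16%; this is a minor correction that changes no conclusion.

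**What to change.** - Ask both arms the same adverse-event question at each existing outcome visit up to week 48, in addition to the question at sessions.
- Telephone any participant who misses a session or withdraws, and ask the same question.
- Have existing staff other than the blinded outcome assessors ask and record it, because an answer about the effects of manipulation could reveal the allocation.
- Report events by arm, both per participant and per session, so that events found outside sessions are counted and exposure remains visible.
- Correct the prior rate for 18 of 112 to 16%.

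The cost is a few extra minutes per visit, some telephone calls and an additional form for existing staff. No new visits are needed. If these routes are already in the full protocol, one added sentence is enough.

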**Discussion:**

This randomised controlled trial is designed to investigate whether the combination of MT and exercise delivers any additional benefits to people with mild COPD compared to exercise alone. The study is designed in response to recommendations from a recent systematic review calling for more research into the effect of MT in the management of COPD.

**Trial registration:**

ANZCTRN, 12614000766617. Registered on 18 July 2014.

**Electronic supplementary material:**

The online version of this article (doi:10.1186/s13063-017-2027-z) contains supplementary material, which is available to authorized users.

## Background

Chronic obstructive pulmonary disease (COPD) is a major cause of chronic morbidity and mortality. It is responsible for a substantial and increasing proportion of the economic and social burden of disease and is currently ranked as the fourth leading cause of death worldwide [1, 2]. The disease is characterised by progressive loss of lung function and includes symptoms such as dyspnea, sputum production and cough [1, 2]. While lung function tests are the primary method used to diagnose and track disease progression, COPD is associated with other comorbidities such as depression, cardiovascular disease and skeletal muscle dysfunction which also influence progression [1].

As exercise capacity is a prognostic indicator in COPD, any skeletal muscle dysfunction that reduces exercise performance can affect disease severity over time by reducing exercise capacity [2]. In COPD, the primary source of exercise limitation is dyspnea, which curtails exercise performance before maximum capacity has been reached. Exercise performance has therefore become a target for therapeutic intervention with both international and Australian guidelines now including exercise training as a standard component in pulmonary rehabilitation [1, 2]. One of the causes of exercise-limiting dyspnea is altered chest wall mechanics which includes an increase in chest wall rigidity (CWR) [3–6]. This increase results in a fall in the efficiency of the ventilatory pumping mechanism and an increase in the effort required to breathe [5, 7–10]. Addressing the increase in CWR has been suggested as a way of reducing or delaying the onset of exercise-limiting dyspnea [11].

The increase in CWR typically seen in COPD is initially the result of expansionary forces exerted on the chest wall by the development of lung hyper-inflation [12]. Over time, this increase is perpetuated by the mechanical properties of the respiratory muscles which resist changes in length through a process known as thixotropy [13, 14]. The thixotropic properties of a muscle are determined by the position that muscle is held in just prior to contraction. In the case of the respiratory muscles, lung hyper-inflation places these muscles in either a shortened or lengthened position prior to contraction. Altering the resting length of these muscles would reduce CWR and therefore mitigate one of the factors responsible for producing exercise-limiting dyspnea.

## Methods/design

### Study design

The trial is designed as a randomised controlled trial and fulfils the requirements of the Standard Protocol Items: Recommendations for Interventional Trials (SPIRIT) checklist [21] (Additional file 1). It will evaluate 202 participants randomly allocated to two equal groups. Participants in Group 1 (Ex) will undergo an exercise regime that has been modelled on an existing pulmonary rehabilitation program; participants in Group 2 (SM + Ex) will have MT which includes SMT administered to their thoracic spine and ribs just prior to performing the same exercise regime as Group 1. Participants will be recruited through direct referral from their respiratory specialist or general practitioner or through self-referral in response to public advertisements calling for volunteers for the trial. The trial is being conducted in the pulmonary rehabilitation department at Sutherland Hospital in Sydney, Australia.

### Participant characteristics

The trial includes both males and females between the ages of 50 and 65 years of age with a forced expiratory volume in the 1^st^ second (FEV_1_)/forced vital capacity (FVC) ratio of < 0.7 and an FEV_1_% predicted of 60–80% (COPDX 2016: mild COPD). Participants will be excluded if they are currently smoking, cannot complete a 6-minute walking test (6MWT) unassisted, have a history of autoimmune disease or are contra-indicated to SMT. Inclusion and exclusion criteria are described in Table 1.

**Table 1 Tab1:** Inclusion and exclusion criteria for participation

Inclusion criteria	Exclusion criteria
• Male and female • 50–65 years • Mild COPD (60% ≤ FEV_1_% < 80%: COPDX) • Stable COPD (no exacerbations in preceding 6 months) • Non-smoking (for preceding 6 months) • Willingness to provide written consent • Willingness to participate in and comply with the study requirements	• Inability to complete 6-minute walking test unassisted • History of auto-immune disease, e.g. RA or SLE that may have altered systemic inflammatory biomarkers • Contra-indicated to thoracic spinal manipulation o Bone density (DEXA) scores below minimum levels (T score < –2.5 and/or Z score < –1) o Thoracic joint instability o Acute pain on thoracic joint range of motion testing o Advanced chest wall muscle wasting o High level of anxiety related to receiving thoracic spinal manipulation • Inability to understand English • Inability to provide informed consent, e.g. people with a cognitive impairment, an intellectual disability or a mental illness • Completed a PR program in the previous 12 months

*COPD* chronic obstructive pulmonary disease, *COPDX* the COPD-X Plan. Australian and New Zealand guidelines for the management of chronic obstructive pulmonary disease. Version 2.45. March 2016, *FEV*
_*1*_
*%* forced expiratory volume in the 1^st^ second percent predicted (age-matched), *RA* rheumatoid arthritis, *SLE* systemic lupus erythematosus, *DEXA* dual energy X-ray absorptiometry, *PR* pulmonary rehabilitation

### Protocol description

Volunteers who meet the inclusion criteria will be given an information sheet and asked to provide written consent to participate in the trial. They will then undergo a physical screening examination for the presence of contra-indications to thoracic MT. After successfully passing this screening, they will be enrolled in the trial, given a trial-specific identification (ID) number and allocated to a group sequentially using a computer-generated random sequence list drawn up prior to the start of the trial by a member of the staff not involved in any other aspect of the trial. Baseline measurements for each participant are then taken. These include lung function assessment using spirometry, exercise capacity (6MWT), chest wall expansion (tape measure), quality of life (St George’s Respiratory Questionnaire: SGRQ), anxiety and depression levels (Hospital Anxiety and Depression Scale: HADS) and systemic inflammatory biomarker levels via blood sampling (C-reactive protein (CRP) and leukocyte count). The study protocol flow of participants is outlined in Fig. 1.

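### Allocation is placed before the baseline measurements that serve as the ANCOVA covariate, and the groups cannot have been matched on values not yet taken

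*Protocol article*

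**What the plan says.** The Protocol description sets out one sequence. "Volunteers who meet the inclusion criteria will be given an information sheet and asked to provide written consent". "They will then undergo a physical screening examination for the presence of contra-indications to thoracic MT". Those who pass are enrolled, given an ID number and "allocated to a group sequentially using a computer-generated random sequence list drawn up prior to the start of the trial". Only after that: "Baseline measurements for each participant are then taken". The list that follows begins "These include lung function assessment using spirometry, exercise capacity (6MWT), chest wall expansion (tape measure" and goes on to SGRQ, HADS, CRP and leukocyte count.

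Three other places bear on this:

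- Statistical analysis: "Analysis will be performed as an analysis of covariance (ANCOVA) for differences between groups with baseline as a covariate".
- Abstract, Methods/design: "The cohort will be divided into two equal groups matched at baseline".
- Table 1, exclusion criteria: "Inability to complete 6-minute walking test unassisted", with no timing given.

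The text after Fig. 1 says that outcome assessors and the nurse who draws blood are blinded to allocation. Blinding of participants is not mentioned.

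**The concern.** ANCOVA on baseline estimates the treatment effect without bias when the covariate cannot have been influenced by the arm. A value recorded before allocation has that property by construction. A value recorded after allocation has it only if allocation changed neither the measurement nor who provided it.

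Here one arm is to receive hands-on therapy of about 20 minutes per session and the other is not. Spirometry and the 6MWT depend on effort, and SGRQ and HADS are self-reported. Blinding the assessor does not protect these measures if the participant knows the arm. Table 1 itself treats the prospect of manipulation as something that can provoke anxiety, since it excludes people highly anxious about it; yet baseline HADS is taken after allocation. Someone who leaves between allocation and baseline would have neither covariate nor outcome, which leaves the planned multiple imputation little to work with.

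Separately, the claim of matched groups cannot be squared with the described procedure, whatever one thinks about bias.

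**Working it through.** **1. Order of steps.** Read in sequence, the Protocol description gives: inclusion criteria met; consent; examination for contra-indications; enrolment and allocation; baseline. Nothing in the visible text reverses the last two. Figs. 1 and 2 are not shown. The Statistical analysis section names baseline as the covariate, and the only full set of baseline measurements described is the one taken after allocation.

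**2. Size of a possible bias.** The adjusted effect is (follow-up difference) − slope × (baseline difference). If knowing the arm moves the mean baseline in one arm by d and leaves follow-up unchanged, the adjusted effect moves by slope × d in absolute value. The sign depends on which arm moves and in which direction. The documents give neither the slope nor d, so both are assumptions. The 200 mL target for FVC is from Sample size calculation.

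| Assumed shift d | Slope 0.7 | Slope 0.9 | Share of 200 mL |
|---|---|---|---|
| 0 mL | 0 | 0 | 0% |
| 25 mL | 17.5 mL | 22.5 mL | 9–11% |
| 50 mL | 35 mL | 45 mL | 18–23% |

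**3. Matching.** A list drawn up before the trial and used before baseline is measured cannot match groups on those baseline values. Randomisation gives balance only in expectation. For scale, the protocol prints no SD, so I back-calculated one from its 92 per group, assuming a two-sided alpha of 0.05, 80% power and a simple comparison of two means:

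SD = 200 / [(1.960 + 0.842) × √(2/92)] ≈ 484 mL.

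If that is also the SD of baseline FVC (an assumption), then with 101 per arm the chance baseline difference has SE = 484 × √(2/101) ≈ 68 mL, a 95% range of about ±134 mL. Such chance imbalance does not bias the comparison, but it is not matching.

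**4. The 6MWT exclusion.** The only pre-treatment 6MWT described is the baseline one, which follows allocation. The text does not say whether another is done earlier.

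**5. Precision of an analysis without the covariate.** On the same back-calculated SD and 92 per arm, the SE of an unadjusted difference is 484 × √(2/92) ≈ 71 mL. That is larger than any bias in the table, so such an analysis can reveal a large distortion but cannot rule out a small one.

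The point changes no sample-size figure.

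**The case against.** The strongest reply is that allocation is not disclosure. The article does not say when participants learn their arm. Baseline precedes treatment, and if the arm is still concealed at that time, a covariate measured after allocation does no harm. This stands, and it is why the bias range includes zero. It does not remove the point, because the text states the risky order and no safeguard for participants.

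A reader might infer that people are being excluded after randomisation for failing the 6MWT, in conflict with the intention-to-treat analysis. The documents do not establish this. The Protocol description plainly abbreviates screening: FEV₁ % predicted must be known for the inclusion criteria to be met before consent, and bone density is among the contra-indications, yet neither test is described there. A screening 6MWT may exist too. What can be said is that the timing is not given.

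A reader might also infer that every outcome model is affected. That goes too far. Exacerbation frequency is a secondary outcome but is not in the baseline list, and CRP and leukocyte count are neither effort-dependent nor self-reported.

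Finally, the matching phrase may be loose wording for expected balance, since Study design speaks only of random allocation to equal groups. An article may also leave blocking or stratification to the full protocol, and a list stratified on screening FEV₁ % predicted would have been possible. That is fair, but it would be stratification on a screening value, not groups matched on baseline, and the article describes neither.

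**Conclusion.** The concern holds as a matter of stated order: allocation comes first, and the ANCOVA covariate is measured afterwards in participants whose blinding is not stated. This is a risk of bias, not a demonstrated bias. It materialises only if participants know their arm at baseline and this changes their performance, their answers or their attendance. Its size is zero without a shift and about 18 to 45 mL of FVC under the assumed shift of 25 to 50 mL and slope of 0.7 to 0.9; none of those inputs comes from the documents. The conflict between the abstract's matching claim and the allocation procedure rests on no assumption about bias. The timing of the 6MWT exclusion is unclear rather than shown to be wrong.

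**What to change.** 1. In Protocol description, change the order so that all eligibility checks, including the 6MWT, and all baseline measurements are completed and recorded before the next allocation is made or revealed. If this is already the practice, say so.
2. In the abstract, replace the matching claim with a statement that participants are randomly allocated to two groups of equal size. Stratifying the list is an option, not a necessary correction.
3. For participants already allocated before baseline, add a sensitivity analysis of the primary outcome without the baseline covariate. A shifted baseline cannot affect that comparison, but it is less precise and does not repair arm-dependent loss between allocation and baseline. Report by arm how many were allocated but gave no baseline.

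The cost is small: no additional outcome measurement, a re-ordering of two steps, and one extra analysis. Some people may complete baseline tests and then prove ineligible. Recruitment was still ongoing when the article was submitted. For anyone already allocated before baseline, the order can no longer be changed, and only the third step and the corrected wording help.
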